### Statistical analyses

Descriptive statistics are used to describe the study population at the two time points in the evaluation study (baseline and 12 month follow-up). Baseline variables are compared to detect differences between patients and professionals in the intervention group (FFF approach) and control group (care as usual). To assess baseline differences between the groups we use unpaired Student’s t-tests (continuous variables with normal distributions), Mann-Whitney U-tests (continuous variables with non-normal distributions) and Chi-square tests (categorical variables). Effect analyses are performed based on the intention-to-treat principle. Analyses of outcomes are performed by means of univariate, multivariate, and multilevel methods (to account for the nested structure of the data). To analyze the differences in outcomes between the intervention group and control group, we employ linear mixed model with random effects (multilevel analysis). To estimate the effects of the FFF approach after 12 months a difference in differences model will be used followed by a sensitivity analysis method specifically developed for difference in differences model based on more general methods of bounds developed by Rosenbaum [138]. Potential confounding and effect modification is accounted for when performing the analyses and, if necessary, adjustments for baseline differences are made. To handle missing data multiple imputation techniques will be used. Ultimate goals of these analyses are to test the assumptions of the theoretical framework with the instruments described in the study protocol. Finally, we will assess clinical relevance of improvements made in cognitions and behaviors among both patients and professionals. The software package IBM SPSS statistics version 23 is used for all statistical analyses.

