### Study design

The longitudinal evaluation study has a mixed methods design in which a combination of quantitative and qualitative research methods are employed in order to evaluate the effectiveness, processes, and cost-effectiveness of the FFF approach. The evaluation study is performed between 2014 and 2017. The study has a matched quasi-experimental design with one pretest and one posttest measurement, i.e. the effects are measured before and after the intervention. Measurements are performed at baseline (T0) and 12 months thereafter (T1). Moreover, the study includes an intervention and a control group (i.e. intervention and control GP practices).

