***Step 3:*** GPs of the intervention group make their own selection of eligible patients to be included in the FFF approach. This selection can be based on the frailty scores obtained by the administration of the self-report TFI questionnaire but can also be based on additional interviews and measures that are performed by the healthcare professional as part of the care provision. Although the TFI is a reliable and valid instrument for measuring frailty in community-living older adults [82, 88], the previously stated added value of other interviews and measures to assess frailty underlines the importance of not relying solely on the TFI as a measure to identify frail older patients [83]. Consequently, patients that are not frail according to the TFI (score ≤ 4) but are considered frail based on other examinations performed by healthcare professionals may nevertheless be selected for the FFF approach.

***Step 4:*** Eligibility of the frail older people selected in Step 3 is then assessed in terms of the inclusion and exclusion criteria by the researchers. For participation in the evaluation study we exclude (1) older people living in nursing homes or homes for the elderly, (2) persons having an estimated life expectancy of less than 3 months, and (3) people with an inadequate understanding of the Dutch language. A challenge in quasi-experimental designs is to reduce the risk of selection bias, i.e. preexisting differences in characteristics between the intervention group and control group due to the absence of random intervention assignment. This may result in a biased posttest measurement. In order to acquire unbiased estimates of the effects, the most important covariables should be balanced between intervention and control groups [89, 90]. To increase comparability of the intervention and control groups, we use one-to-one matching: each individual participant in the intervention group is matched to one participant in the control group with the same values of the key covariables, namely sex (male or female), frailty score (score on the TFI), and educational level (high or low). This one-to-one matching is performed by the researchers.

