### Sample size

We aim to include 500 frail older patients (250 patients of intervention GP practices and 250 patients of control GP practices). We aim to optimize participation by means of personal home visits, however, we anticipate a drop-out rate of approximately 20% between T0 and T1 (e.g. due to death, refusal). Accordingly, we expect 400 patients at T1 in the intervention and control groups. Sample size calculations are based on the mean well-being score (SPF-IL) of a comparable Dutch population of frail community-dwelling older persons (N=945) [137]. To detect a mean improvement in well-being of 1/4 standard deviation (SD) based on the SPF-IL, we need at least 198 older patients in each group (based on a mean SPF-IL score of 2.56 [SD = 0.45]; alpha (two-sided) = 0.05, beta = 0.20, ratio 1:1).

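### Patients are matched one-to-one, but the stated analysis does not carry the matching: baseline tests are unpaired and nothing secures the matching variables in the outcome model (probably a small, conservative loss)

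*Protocol article*

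**What the plan says.** All references are to the protocol article.

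- **Study design:** "The study has a matched quasi-experimental design with one pretest and one posttest measurement".
- **Participants and recruitment, Step 4:** "each individual participant in the intervention group is matched to one participant in the control group with the same values of the key covariables". The key covariables are sex, TFI score and education (high or low). The stated purpose is comparability of the groups.
- **Statistical analyses, baseline:** "To assess baseline differences between the groups we use unpaired Student’s t-tests (continuous variables with normal distributions". Mann-Whitney and chi-square tests are named for other variable types. These comparisons cover both patients, who are matched, and professionals, who are not.
- **Statistical analyses, outcomes:** "Analyses of outcomes are performed by means of univariate, multivariate, and multilevel methods (to account for the nested structure of the data". The between-group analysis is a linear mixed model whose random effects are not listed. A difference-in-differences model and a Rosenbaum-type sensitivity analysis follow. Confounding is to be accounted for, and baseline differences are adjusted for only where needed.
- **Sample size:** "we need at least 198 older patients in each group", with "alpha (two-sided) = 0.05, beta = 0.20, ratio 1:1". No within-pair correlation appears.

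**The concern.** The design creates a dependence that the stated analysis does not mention. Three features of the text combine.

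1. Unpaired tests for matched patients are a positive choice, not an omission. If pair members resemble each other on a baseline variable, these tests are conservative and can miss imbalance, in a study that itself names selection bias as a major concern.
2. A pair joins patients from two different practices, so it crosses the nesting that is the only reason given for multilevel methods.
3. Adjustment depends on baseline differences. Sex, TFI score and education are balanced by construction, so a rule triggered by differences would tend to leave them out.

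At stake is some precision in the primary SPF-IL comparison and the reliability of the baseline balance check. False positives are not inflated.

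**Working it through.** **Inputs from the article.** Effect: "To detect a mean improvement in well-being of 1/4 standard deviation (SD) based on the SPF-IL". SD: "based on a mean SPF-IL score of 2.56 [SD = 0.45", so the effect is 0.45/4 = 0.1125 points, or 0.25 SD. Two-sided alpha is 0.05. Enrolment is 250 per group with 20% drop-out, leaving 250 × 0.8 = 200 per group at T1.

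**Inputs assumed.** The within-pair correlation of 12-month change (ρ) is not given; I use 0.05 to 0.2. The SD of change is not given either. It equals SD × √(2(1 − r)), so using the score SD assumes a T0–T1 correlation r of 0.5.

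**The plan's own figure.** For independent groups, n = 2(z_alpha + z_power)²/0.25².
- Two-sided: 2 × (1.960 + 0.842)² × 16 ≈ 251.2, so 252.
- One-sided: 2 × (1.645 + 0.842)² × 16 ≈ 197.8, so 198.

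The stated 198 therefore reproduces only with one-sided alpha. That is a separate matter. What counts here is that it is an independent-groups figure with no credit taken for matching.

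**Cost of ignoring the matching** (SD units, practices ignored):
- SE used if the matching is ignored: √(2/200) = 0.100
- True SE: √(2(1 − ρ)/200)
- Power using the matching: Φ(0.25/SE_true − 1.96)
- Power ignoring it: Φ((0.25 − 1.96 × 0.100)/SE_true)
- Actual two-sided error rate if ignored: 2(1 − Φ(1.96 × 0.100/SE_true))

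| ρ (assumed) | SE_true | SE too wide by | Power ignoring | Power using | Actual error rate |
|---|---|---|---|---|---|
| 0 | 0.1000 | 0% | 70.5% | 70.5% | 0.050 |
| 0.05 | 0.0975 | 3% | 71.0% | 72.7% | 0.044 |
| 0.1 | 0.0949 | 5% | 71.5% | 75.0% | 0.039 |
| 0.2 | 0.0894 | 12% | 72.7% | 79.8% | 0.028 |

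**Practice clustering shrinks the excess width.** With 11 and 4 practices the mean cluster sizes are 200/11 = 18.2 and 200/4 = 50. The design effects 1 + (m − 1)ICC are 1.17 and 1.49 at an assumed ICC of 0.01, and 1.86 and 3.45 at 0.05. The ratio of SEs is √(S/(S − 2ρ)), where S is the sum of the two design effects. At ρ = 0.1:
- ICC 0.01: √(2.66/2.46) = 1.040
- ICC 0.05: √(5.31/5.11) = 1.019

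The 5% excess becomes about 4% and 2%.

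**Why interaction with time.** In a difference in differences, a pair intercept or a main effect of a fixed baseline variable cancels. Only terms that vary with time can recover precision.

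**Why complete pairs is not the remedy.** If drop-out is independent within pairs, 0.8 × 0.8 = 64% of pairs survive: 160 of 250. Power on 160 pairs is 65.4% at ρ = 0.1 and 70.5% at ρ = 0.2, below the 71.5% and 72.7% from ignoring the matching with 200 per group.

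**The case against.** The unpaired tests are named only for baseline comparisons; no unpaired test is named for any outcome. A reader might infer that the primary comparison discards the pairs, so that its intervals and power contradict the design. The article does not support this. The random effects are not listed, a pair or stratum term is compatible with the text, and an article commonly leaves such detail to a fuller plan. Confounding is also to be accounted for, which could bring in the matching variables. That part of the objection stands.

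It also stands that a pair term is not required. TFI score runs from 0 to 15, so the matching defines at most 2 × 16 × 2 = 64 cells for 250 pairs, and who is paired with whom inside a cell is arbitrary. Adjusting for the three variables captures the similarity that matching creates. Nor does the article claim a power gain: it gives comparability and reduced selection bias as the purpose.

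A reader might also expect a large loss. At ρ = 0.5 the formulas give intervals 41% too wide and 78% v 94% power. That would need sex, TFI score and education to explain about half the variance in 12-month change, which nothing in the article supports.

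The objection does not dispose of two points. Unpaired tests are prescribed for matched patients, and the conditional adjustment rule does not secure the matching variables in the model.

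**Conclusion.** The point holds as a mismatch between the stated design and the stated analysis, not as proof that the primary analysis is invalid. The baseline part rests on explicit text. The outcome part rests on what the text fails to secure: nesting is the only reason given for the mixed model, and adjustment is conditional. The article does not say what triggers adjustment; I take differences at baseline as the natural reading.

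If the matching is ignored, the consequence is conservative. Over ρ of 0.05 to 0.2 the loss is roughly 2 to 7 percentage points of power, and the low end is the more plausible for change scores. At ρ = 0 nothing is lost. These figures assume a T0–T1 correlation of 0.5 and ignore practices; with clustering the excess SE is smaller. The larger difficulty with 198 per group, that it matches one-sided alpha and makes no allowance for practices, has a different cause and should not be attributed to the pairing.

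**What to change.** In Statistical analyses:

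1. State that the SPF-IL difference-in-differences mixed model always includes sex, TFI score and education, each with its interaction with time, alongside the practice effects and regardless of any baseline test. A pair-by-time random effect crossed with practice is an acceptable alternative.
2. State that patients whose partner drops out stay in the analysis.
3. For matched patients, replace the unpaired baseline tests with standardised differences or paired tests (paired t, Wilcoxon signed-rank, McNemar). Keep unpaired tests for professionals.

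The cost is a few sentences and a few model terms. The matching variables are already recorded for Step 4. The gain is small if they barely predict change, and a pair-by-time variance, if chosen instead, may be estimated as zero.

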### Timeline

Figure 2 shows a general timeline of the data collection among older adults and healthcare professionals, the analyses of the data and writing up the results of the evaluation study.

**Fig. 2 Fig2:**
[figure not shown]
Timeline

## Discussion

Integration of health services is increasingly advocated as a means to develop more effective models of care and improve patient outcomes [37]. Much research in the field of integrated care for community-dwelling older adults has been conducted, however, these innovative interventions have had mixed effects on patient outcomes and there is a need for in-depth evaluations. This underlines the importance of sound theory-based evaluations of integrated primary care approaches. Consequently, in efforts to evaluate the effects of innovative integrated care approaches, insight into the underlying mechanisms explaining the (lack of) effectiveness of these complex multicomponent interventions is crucial. The present paper describes the design of a theory-based evaluation of a proactive integrated primary care approach to improve well-being among frail community-living older adults.

### Strengths and limitations

A major strength of the study is the comprehensive and rigorous evaluation of the complex multicomponent integrated care approach FFF. We use a combination of quantitative and qualitative research methods and assess not only the effectiveness of the approach on frail older persons’ well-being, but also the cost-effectiveness and processes. Selected outcome measures are based on the theoretical model, which facilitates a sound theory-based evaluation. We ultimately may reveal crucial underlying mechanisms of this integrated care approach. Therefore, the theory-based evaluation study is expected to contribute to the existing evidence on improvements in quality of care and patient outcomes, and a better understanding of explanatory mechanisms underlying integrated primary care approaches.

The proposed evaluation study has potential limitations and challenges. First, the absence of randomization makes the design more susceptible to bias [139]. Especially selection bias is a major concern in non-randomized studies. Systematic differences between the groups result in incomparable groups which ultimately may lead to biased estimates of the intervention effect [140]. To reduce the impact of this bias on the outcome measures studied, we aim to control for important factors in the analysis of the data and by means of matching [141]. To ensure that the intervention and control groups are similar for key covariables, we use one-to-one matching to balance groups instead of matching on a higher level (at healthcare practice level). Moreover, when necessary we use case-mix adjustments to take into account important dissimilarities. However, it is stated by Deeks and colleagues [140] that the degree to which techniques can sufficiently adjust for differences between the groups is still unclear, which ultimately provides no guarantee for unbiased study results [140]. In addition, unknown and unmeasured factors can still influence the outcome [142]. Second, the design of the study makes it impossible to blind participating healthcare professionals and frail older patients. Knowledge of the status of the person (receiving either the FFF approach or care as usual) may have an influence on the responses and may affect compliance [143]. Nevertheless, the interviewers that conduct the interviews with frail older persons are kept unaware of the group the person is in (intervention or control GP practice), so that the interviewers collecting outcome data are not influenced by that knowledge. Blinding of the interviewers aids to reduce differential outcome measurements (information bias) [143]. Due to the nature of the evaluation study, however, it is possible that the patient inadvertently reveals his or her status during the interview (e.g. disclosing information that is specific to the FFF approach). Third, one of the core challenges of the evaluation study is the willingness of frail community-dwelling older patients to participate in the study, especially in the long-term. Recruitment of appropriate numbers of patients requires a sufficiently long period [144]. We aim to optimize participation in the evaluation study by means of home visits instead of interviews over the telephone, recruiting interviewers that live in the same region as the older adults, and sending letters to older patients on behalf of their own GP. Fourth, although control GP practices continue to provide usual care, GPs in the control group may start initiatives to improve care delivery for frail older patients. We collect data on various interventions that are implemented to improve care for older adults and we monitor and describe the activities performed by the GPs. In contrast to the intervention GP practices, control practices are not supported financially by the health insurers to implement elements of the FFF approach. Fifth, recall bias may potentially affect our study findings. Earlier research using a 12 months period of asking patients about their healthcare visits show both under-reporting and over-reporting effects [145]. Administrative data could be included to accurately capture resources for an economic evaluation (if filled in correctly). Sixth, while we included patients and professionals in our theoretical framework and study protocol we did not include informal caregivers. Given their important role in supporting community-dwelling frail older people they are expected to influence the well-being of older persons as well. Given the complexity of the theoretical framework as presented in this paper we decided to first unravel the underlying mechanisms in the relationship between quality of care, cognitions and behaviors of patients and professionals and older persons’ well-being. Future research should look at the role of informal caregivers and their cognitions and behaviors as well. It may be easier to improve outcomes if the patient’s partner is a good self-manager with a positive frame of mind compared to a partner who is depressed, has low self-efficacy and poor investment behavior.

## Abbreviations

ACIC-S: Assessment of Chronic Illness Care Short version
CCM: Chronic Care Model
COPD: Chronic Obstructive Pulmonary Disease
EQ-5D-3L: EuroQol (5 dimensions and 3 levels)
FFF: Finding and Follow-up of Frail older persons
GP(s): General practitioner(s)
ICER(s): Incremental cost-effectiveness ratio(s)
Katz ADL index: Katz Activities of Daily Living index
MMSE(-12): (12-item) Mini-Mental State Examination
PACIC-S: Patient Assessment of Chronic Illness Care Short version
QALY(s): Quality-Adjusted Life-Year(s)
SD: Standard deviation
SF-20: 20-item Short Form Health Survey
SFSPC-model: Model for reporting on Somatic, Functional, Social, Psychological, and Communicative indications
SMAS-S: Self-Management Ability Scale Short version
SPF-IL: Social Production Function Instrument for the Level of well-being
TFI: Tilburg Frailty Indicator
